## 2) INTRODUCTION (IRAS A6-1)

### Lay Summary

During pregnancy women may need or choose to undergo physical therapies such as physiotherapy, massage or osteopathy. Recent findings from studies of mothers who had a stillbirth in late pregnancy found that the position in which women went to sleep in was linked to stillbirth, as was the frequency of day time naps. This link is thought to be due to changes in mother's blood flow from her heart when lying flat leading to changes in the amount of oxygen going to her baby. This raises concerns that spending extended periods laid flat could be detrimental to baby's health. However, it is not known whether lying flat for extended periods for physical therapies could also alter a baby's heart rate or levels of oxygen. One small study of 33 women from Brazil found that there were no differences in a mother's heart rate, blood pressure, oxygen saturation or baby's heart rate. But there were changes in mother's breathing rate and systolic blood pressure when a mother laid on her front. All the women reported feeling comfortable lying flat (on a bent surface). However, in this study women only spent 6 minutes in each position which is less than a woman would be expected to spend lying in a position for a session of physical therapy. We plan a study to assess whether using a device to support a prone position (Anna cushion) would be associated with changes in mother's heart rate, blood pressure, breathing rate and blood oxygen levels and baby's heart rate. We will also ask about mother's levels of comfort while she is laid in the prone position. The findings of this study will give an indication whether supporting a mother to lie in a prone position for physical therapies is safe and comfortable.

### Scientific Summary

Women frequently experience lower-back or pelvic pain during pregnancy. This may lead to a need for physical therapies such as physiotherapy, osteopathy or massage in late pregnancy. Several case-control studies, and a recent individual patient data meta-analysis has demonstrated an association between going to sleep position and late stillbirth (a greater than 2-fold increased risk with going to sleep supine) and increased frequency of daytime naps. This is thought to be related to maternal haemodynamic changes when a mother lies supine in late pregnancy which decreases cardiac output and uterine blood flow. These changes are accompanied by alterations in fetal behaviour which are consistent with a reduction in oxygenation. This observation raises concerns that spending extended periods laid flat could be detrimental to baby's health. However, it is not known whether lying flat for extended periods for physical therapies could also alter a baby's heart rate or levels of oxygen. One small study of 33 women from Brazil which randomised the order of maternal positions found that there were no differences in a mother's heart rate, blood pressure, oxygen saturation or baby's heart rate between a supine, lateral and prone position (bent over a concave couch). However, there were observed changes in mother's breathing rate and systolic blood pressure when a mother laid on her front. Nevertheless, all the women reported feeling comfortable lying flat (on a bent surface). However, in this study women only spent 6 minutes in each position which is less than a woman would be

expected to spend lying in a position for a session of physical therapy. Therefore, further work is required to determine whether spending extended periods laid prone is safe for mother and baby.

The co-investigator ([name]) has developed a device to support mothers in a prone position (Anna cushion). This study will investigate whether adopting this position supported by Anna cushion is associated with changes in mother's heart rate, blood pressure, breathing rate and blood oxygen levels and fetal heart rate as assessed by the cardiotocograph. We will also ask about mother's levels of comfort while she is laid flat. The findings of this study will give an indication whether supporting a mother to lie in a prone position for physical therapies is safe and comfortable

### **3) BACKGROUND (IRAS A12)**

The association between maternal position and cardiac output has been known for many years [1]. More recently, studies have demonstrated an association between the position in which a mother goes to sleep and late stillbirth (after 28 weeks) [2-6]. This has been consistently demonstrated in five studies from four different countries. Furthermore, there is an association between the frequency of daytime naps and the risk of late stillbirth [2, 3]. This is hypothesised to be due to frequent exposure to a supine sleeping position. When a mother lies flat there is a reduction in cardiac output and consequent uterine blood flow, this is due to compression of the inferior vena cava by the gravid uterus [1, 7]. These changes are associated with alterations in fetal behaviour consistent with a reduction of fetal oxygenation [8]. Whilst sleep is associated with extended periods spent in specific positions little is known about the effect of maternal position for other purposes in late pregnancy.

One study of maternal position exposed 33 women to a supine, lateral and prone positions in a random sequence [9]. To maintain a prone position woman used a concave stretcher designed. This study adopted each position for 6 minutes following a 10-minute period of adjustment to the experimental surroundings. This study found no differences in a mother's heart rate, diastolic blood pressure, oxygen saturation or baby's baseline heart rate between supine, lateral and prone positions (bent over a concave couch) [9]. However, there were changes in mother's respiratory rate and systolic blood pressure when a mother laid prone. Nevertheless, all the women reported feeling comfortable lying flat (on a bent surface). A more recent study of 50 healthy pregnant women and 15 women with preeclampsia found that lying in a prone position for 5 minutes prior to observations was associated with a reduction in systolic blood pressure, which for women with preeclampsia could be beneficial [10]. Importantly, there have not been any studies investigating a more clinically meaningful timeframe of exposure of adopting a supine position for physical therapies e.g. 30 minutes. Therefore, further studies are required.

Clearly, maintaining a prone position for physical therapies in late pregnancy is difficult due to the gravid uterus. Co-investigator ([name]) has developed a device for to support mothers in a prone position

(Anna cushion). Anna cushion (Figure 1) is designed to allow pregnant women to lie safely and comfortably in a prone position up until the end of their pregnancy. Anna cushion itself is specifically moulded from of a medical grade, medium density, closed cell foam, which has been covered in a double layer of cotton interlock fabric. The height of the cushion is 15cm, with the inner section having been cut out and contoured to support the pregnant abdomen. The fabric covering has enough stretch to support the abdomen, whilst not restricting movement in any way. The length of the cushion is 68 cm, with tapered caudal and distal ends, to allow the woman to lie comfortably, without any unnecessary pressure exerted on the chest or hips.

[figure not shown]

**Figure 1 Anna cushion**

[figure not shown]

The patient positions themselves over Anna cushion, placing their hands/arms in front of the cushion, their bump over the middle section of the cushion and their knees behind the cushion.

[figure not shown]

The patient lowers themselves down carefully so that their bump falls neatly in the middle of the carved-out section, their breasts touching the top end of the cushion, and the top of their legs resting on the bottom end of the cushion.

**Table 1** How to use Anna cushion

The proposed study will investigate whether adopting this position supported by Anna cushion for a clinically meaningful timeframe is associated with changes in mother's heart rate, blood pressure, cardiac output, breathing rate and blood oxygen levels and fetal heart rate as assessed by continuous cardiotocography. We will also ask about mother's levels of comfort while she is laid flat. The findings of this study will give an indication whether supporting a mother to lie in a prone position for physical therapies is safe and comfortable.

#### **4) STUDY OBJECTIVES**

##### **4.1 Primary Question/Objective: (IRAS A10)**

To describe the cardiorespiratory effects for a mother maintaining a prone position supported by the cushion (Anna cushion) for a period of 30 minutes.

##### **4.2 Secondary Question/Objective: (IRAS A11)**

To determine whether maintaining a prone position is associated with any effects on the fetal heart rate, and to determine whether using a device to support a prone position is comfortable for the mother.

#### **5) STUDY DESIGN & PROTOCOL**

##### **5.1 Participants (IRAS A15)**

We will conduct a cohort study of women with a viable singleton pregnancy over 28 weeks' gestation.

##### **5.2 Study Intervention and/or Procedures (IRAS A13, A18, A19)**

Prior to commencing the study women will be asked to complete a short questionnaire about their pregnancy which will ask about symptoms of pain or discomfort, their anxiety levels and prior knowledge and experience of maternal position during sleep or rest. They will then have fetal and maternal monitoring connected via a series of self-adhesive electrodes. The fetal heart rate and uterine activity will be monitored using the MONICA AN24 system which has been used previously by our group to monitor fetal heart rates for extended periods [11]. This involves application of five self-adhesive ECG electrodes to the maternal abdomen (Figure 2).

[figure not shown]

Figure 2 – MONICA AN24 fetal monitoring system showing electrodes applied to

Maternal cardiac output, heart rate and blood pressure will be measured by the Cheetah NICOM system which has self-adhesive electrodes applied to the maternal back and a blood pressure cuff to the maternal upper arm. The NICOM system has previously been validated for use in pregnancy [12]. A pulse oximetry probe will be applied to the left forefinger. The mother will be asked to lie

on her left-hand side (the optimal position for maternal and fetal wellbeing) for 20 minutes with observations recorded at 5-minute intervals on to a case report form.

If any of the maternal or fetal values are outside of the anticipated range the experimental protocol will be discontinued. Women who have hypertension (>140/90 mmHg), tachycardia (>110 bpm), tachpnoea (>20 breaths per minute) or abnormal fetal heart rate traces will be referred to the maternity service for further assessment. A transfer letter template has been devised to rapidly report problems to the receiving medical team.

If the maternal and fetal observations are normal during the period spent in left lateral position the mother will be positioned in the prone position on the device for a period of 30 minutes. During this time observations recorded at 5-minute intervals on to a case report form. If at any point the mother feels unwell or the observations become abnormal (as outlined above) the experimental protocol will be ceased and the mother returned to a left lateral position. If there are persistent abnormalities of the fetal heart rate trace the mother will be referred urgently to the maternity service.

Following a 30-minute period in the prone position participants will then be returned to the left lateral position for 20 minutes of further monitoring with observations recorded at 5-minute intervals. After this period the monitoring will be disconnected and the electrodes removed. The site will be checked for signs of skin irritation. Women will then be asked to complete a short questionnaire to describe their experience of using the device and a final survey of their anxiety levels. Women will then be given a small token of thanks for their participation.

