### **Primary Outcome Measure**

Maternal cardiac output as assessed by non-invasive cardiac monitoring.

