### **Secondary Outcome Measures**

A variety of other measures of maternal cardio-respiratory status will be measured, including: heart rate, blood pressure, respiratory rate and oxygenation via pulse oximetry.

Fetal wellbeing assessed by continuous cardiotocography which will report baseline heart rate, variability, the presence of accelerations or decelerations.

Acceptability, including maternal anxiety, will be assessed using standardised measures and comfort using a user-completed questionnaire.

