## **9) STATISTICAL CONSIDERATIONS**

### **9.1 Statistical Analysis (IRAS A56, A62)**

Data regarding maternal characteristics will be analysed using descriptive statistics. Data regarding maternal cardiac output in different maternal positions will initially be evaluated to determine whether values are normally distributed. Depending on the distribution of values, they will be transformed to a normal distribution if appropriate and a repeated measures ANOVA performed. If they are not normally distributed and transformation does not achieve a normal distribution a Friedman test will be performed. This approach will address variation between individual participants.

Descriptive and comparative statistical analysis will be conducted in STATA (STATACORP, TX, USA). As the investigators anticipate some variation in the baseline observations between participants both raw values and change from baseline status will be evaluated.

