## **11) SAFETY CONSIDERATIONS AND ADVERSE EVENTS (IRAS A75-1, A75-2)**

Prior studies suggest that lying prone does not have adverse consequences for mother or baby. However, it is possible that a mother may develop symptoms, have deviations from blood pressure or that the fetal heart rate trace would become abnormal. If these situations develop during the experimental protocol the procedure would be stopped and the mother transferred to a left-lateral position to allow a period for the abnormal symptoms or observations to resolve. The mother would be clinically assessed by the research midwife, if symptoms or abnormal observations do not resolve the mother would be transferred to the maternity department at St Mary's Hospital for further management. A handover would be given to the clinical staff by the research midwife looking after the participant. The need to terminate the protocol would be recorded in the study and reported in the final analysis.

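### Prone sessions stop according to how the woman reacts, but the named tests usually need complete data, so stopped women may be lost from or unevenly represented in the cardiac output comparison

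*Protocol*

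**What the plan says.** **Stopping.** Section 5.2 says of the prone phase: "If at any point the mother feels unwell or the observations become abnormal (as outlined above) the experimental protocol will be ceased". The limits it points back to are in the same section: "Women who have hypertension (>140/90 mmHg), tachycardia (>110 bpm), tachpnoea (>20 breaths per minute) or abnormal fetal heart rate traces will be referred". No cardiac output limit is listed.

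**Recording.** For the 30 minutes prone: "During this time observations recorded at 5-minute intervals on to a case report form". The recovery phase is described only for a session that ran its course: "Following a 30-minute period in the prone position participants will then be returned to the left lateral position for 20 minutes of further monitoring".

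**Outcomes.** The primary outcome is "Maternal cardiac output as assessed by non-invasive cardiac monitoring". The secondary maternal outcomes are "heart rate, blood pressure, respiratory rate and oxygenation via pulse oximetry", and the fetal trace is also a secondary outcome.

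**Analysis.** Section 9.1 compares cardiac output between maternal positions, with transformation if needed and "a repeated measures ANOVA performed". The fallback is a Friedman test. No test is named for the vital signs.

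**Terminations.** Section 11 states: "The need to terminate the protocol would be recorded in the study and reported in the final analysis". Section 6.5 keeps data up to the point of consent withdrawal, but it does not deal with a session stopped under section 5.2.

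**The concern.** The amount of prone data a woman contributes depends on how she responds to lying prone. Apart from symptoms, every stopping trigger is also a secondary outcome. The primary analysis uses two tests that, as usually run, have no place for a woman with missing cells.

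Two consequences follow. The cardiac output comparison may leave out the women who reacted, or let a short exposure stand for 30 minutes. And if results are summarised for completers only, a woman in that group cannot have exceeded the listed limits before her last reading. Upward excursions in blood pressure, heart rate and respiratory rate are then trimmed by the design.

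This matters because the study is meant to indicate whether supported prone lying is safe and comfortable. Being unable to finish 30 minutes is direct evidence on that question.

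**Working it through.** **1. Stopping triggers against outcomes.**
- Blood pressure, heart rate, respiratory rate and the fetal trace are both triggers and secondary outcomes.
- Feeling unwell is a trigger only.
- Oxygen saturation is an outcome with no listed limit.
- Cardiac output is the primary outcome with no listed limit. Section 5.2 also stops the preceding left lateral phase for values outside an anticipated range. That could be read to include cardiac output, but no range is given.

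**2. How a stopped woman enters the named tests.** Suppose the first prone reading is at 5 minutes, so a full session has 30/5 = 6 readings, and a woman is stopped after the 10-minute reading with 2 of 6.
- *Factor is time point:* four cells are empty. Friedman cannot rank her block, and a classical repeated measures ANOVA drops her.
- *Factor is period (lateral, prone, recovery):* her recovery cell may be empty, because section 5.2 describes that recording only after 30 minutes prone. Section 11 does return her to left lateral, so a later value is possible but not assured.
- *Factor is position, available prone readings averaged:* she stays in, but 10 minutes of exposure counts the same as another woman's 30.

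Only a woman stopped before her first prone reading certainly has no prone value.

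**3. The plan's own figure.** From section 9.2: fall 6.6 − 5.7 = 0.9 L/min, SD 1.0, 80% power, alpha 0.05 (taken as two-sided).
n per group = 2 × (1.960 + 0.842)² × 1.0² / 0.9² = 19.4, so 20. The stated 20 reproduces (power 81.2%), and this point alleges no error there. The calculation has no allowance for stopped sessions.

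**4. Size if stopped women are dropped (illustrative).** Assumptions, none from the protocol:
- Within-woman correlation of 0.5, so the SD of change is 1.0 × √(2 × (1 − 0.5)) = 1.0 L/min.
- A proportion q is stopped.
- Stopping is driven by a normal variable with correlation r to the fall.

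Expected fall among completers = 0.9 − r × 1.0 × φ(z)/(1 − q), where z is the upper-q normal quantile.
- q = 10%: φ(z)/(1 − q) = 0.195. At r = 0.5, 0.9 − 0.0975 = 0.80; at r = 1, 0.71.
- q = 20%: 0.350. At r = 0.5, 0.725; at r = 1, 0.55.
- q = 30%: 0.497. At r = 0.5, 0.65; at r = 1, 0.40.
- r = 0: 0.90 throughout, so no bias.
- r = −0.5 (stopped women have smaller falls): 0.9 + 0.0975 = 1.00 at 10% and 0.9 + 0.248 = 1.15 at 30%, an overstatement.

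With within-woman correlation 0.3 or 0.7 and r = 0.5, the completer mean is 0.79 or 0.82 at 10% stopped, and 0.61 or 0.71 at 30%.

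**5. Power of a paired test, 20 women (simulated, 40,000 runs, SD of change 1.0).** With none stopped it is 96.8%. At r = 0.5 it is 90.7%, 80.8% and 67.1% for 10%, 20% and 30% stopped. At r = 0 it is 94.6%, 91.4% and 86.4%. Recruiting more women (20/0.9, so 23; 20/0.7, so 29) restores numbers but not the mean.

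**6. What 20 women say about non-completion.** With no stops in 20, the exact two-sided 95% upper limit is 1 − 0.025^(1/20) = 16.8%.

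**The case against.** A reader might infer that the plan is a complete-case analysis that loses every stopped woman. The documents do not say so. Section 9.1 speaks of positions, so a position-level summary is a natural reading and would keep anyone with at least one prone value. A scheduled abnormal reading that triggers a stop can also be on the case report form.

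A reader might also infer that the cardiac output result is certainly biased towards no effect. That is not supported either. Cardiac output is not a listed limit. It is the product of heart rate and stroke volume, so a woman stopped for tachycardia need not be one with a large fall. The protocol's rationale, that reduced cardiac output lowers uterine flow and alters fetal behaviour, makes a link through the fetal trace plausible, but it is stated for supine lying and gives no strength or overall sign.

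Nor can it be said that the vital-sign results will describe completers only: no test or completer summary is planned for them, and section 11 commits to reporting terminations. Women are approached as low-risk and must have normal observations in left lateral first, so stops may be few. Handling of incomplete data often sits in an SAP, which is not at hand here.

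What stands is that the protocol itself names the tests, and in usual form they fit response-dependent stopping badly. Reporting a count of terminations does not correct the cardiac output estimate.

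**Conclusion.** The point holds as a weakness in the chosen analysis, not as a demonstrated bias. Women stopped early may drop out of, or be unevenly represented in, the cardiac output comparison. Any summary confined to women who finished 30 minutes would understate upward blood pressure, heart rate and respiratory rate excursions by design.

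The size for cardiac output cannot be fixed from the documents. With 10% stopped (two women in 20) and r = 0.5, the 0.9 L/min fall shrinks by 0.0975/0.9, about 11%; with 30% stopped, by 0.248/0.9, about 28%. It is nil at r = 0 and reverses if r is negative. These figures rest on assumed stopping rates, an assumed SD of change of 1.0 L/min, normality, and stopped women being dropped altogether. The change is worth making because it is cheap and bears on the study's safety and comfort question.

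**What to change.** In section 9.1:
- Define the analysis set as every woman who begins the prone position.
- Replace the repeated measures ANOVA/Friedman choice with a linear mixed model for cardiac output, with a random effect for woman, that accepts unequal numbers of readings. Use all prone readings recorded up to stopping, including the scheduled reading that triggered it. The transformation step can remain.
- Label readings after return to left lateral as recovery, never as prone.
- Add a sensitivity analysis for the missing prone readings, for example shifting stopped women's unobserved values by a range of pre-stated amounts.

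In section 7, add as a secondary outcome the proportion not completing 30 minutes prone, with reason and exact 95% CI, reported beside the cardiac output result. A woman stopped before her first prone reading has no prone value for the model but counts here.

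The cost is wording and a little more analysis work. The model relies on data missing at random given what it includes. Stopping on a vital sign or the fetal trace, neither of which is in a cardiac output model, may strain that assumption, which is why the sensitivity analysis is needed. No change to the stopping rule or its conduct is proposed.
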